## Abstract

**Background:**

Unintentional injury is a leading cause of childhood morbidity and mortality worldwide. In China, real-world implementation of child injury prevention efforts remains inadequate due to constrained workforce capacity and a lack of operational frameworks.

**Objective:**

This study aims to assess the effectiveness of a mobile health (mHealth) intervention, the Intelligent Child Unintentional-Injury Reduction & Education (iCURE) project, embedded within China’s National Basic Public Health Service Program. The intervention relies on a WeChat (Tencent) service account for caregivers and a web-based platform for health care providers to deliver standardized unintentional injury prevention strategies for young children. Key features of the program include interactive questions and answers, injury risk assessment with instant feedback, a tailored injury prevention knowledge disseminator, and regular reminders to caregivers.

**Methods:**

A double-blind, 12-month follow-up, cluster randomized controlled trial will be implemented in Changsha, Hunan Province, China. Caregivers of children aged ≤5 years will be recruited. Randomization will be conducted at the street or town level. The control group will receive routine safety education, while the intervention group will receive both routine safety education and the iCURE mHealth intervention focused on unintentional injury prevention and delivered via WeChat. Data will be collected at baseline and every 3 months during the study period. The primary outcome is 12-month incidence of unintentional injuries among children, including minor injuries and as reported by caregivers. Secondary outcomes include children’s injury risk level and caregiver supervision behaviors assessed using a standard questionnaire. Data analysis will be conducted using generalized linear mixed models with a Poisson link function and generalized estimating equations to assess the effectiveness of the iCURE intervention, following intention-to-treat principles. Sensitivity analyses will be conducted with per-protocol principles and excluding participants with missing primary outcomes.

**Results:**

As of May 2025, a total of 6701 participants have been successfully enrolled and baseline data were collected for all participants. Of those enrolled, 87.2% (5842/6,701) completed the first follow-up assessment.

**Conclusions:**

This trial will examine the effectiveness of an intelligent mHealth intervention for child unintentional injury prevention building on China’s National Basic Public Health Service Program. If successful, the iCURE intervention may provide a cost-effective strategy for child injury prevention in low- and middle-income countries.

## Introduction

Unintentional injuries remain a leading cause of morbidity and mortality among children worldwide [1]. In 2021, approximately 200,000 children younger than 5 years of age died globally from injuries and 38.7 million experienced nonfatal injuries [2]. In China, where the current research was conducted, injuries were the primary cause of child death in 2021, accounting for 10,827 deaths and 2.15 million incident cases in children younger than 5 years of age [2-4].

Injury prevention frameworks such as the Haddon Matrix and the “4E” model have significantly shaped global policies and interventions over recent decades. Building upon these, the World Health Organization (WHO)’s World Report on Child Injury Prevention (2008) identified key interventions across many domains, including legislation, product safety, environmental modification, education, and emergency care, to reduce major types of child injuries [5]. High-income countries implement many of these strategies through structured programs such as The Injury Prevention Program (TIPP), which offers age-specific safety counseling and pediatrician training to enhance injury prevention practices [6]. However, such resource-intensive approaches require substantial institutional capacity, trained personnel, and long-term funding, posing implementation challenges for low- and middle-income countries (LMICs) such as China.

Chinese health authorities have incorporated injury prevention into the National Basic Public Health Service Program [7], a system whereby health-related information is conveyed to the population through health care providers. Despite its broad coverage, the program faces significant capacity constraints. Primary care providers are often understaffed and overburdened with routine services such as immunizations, chronic disease management, and regular medical examinations [8]. Most practitioners lack training in injury prevention, and the absence of operational guidelines limits implementation [9-11]. Consequently, neither globally recommended programs [5,6] nor technical guidelines [12] developed within China have been implemented in Chinese primary care settings.

Recognizing the potential of digital health as an alternative to deliver health-related messaging to parents and families, both the WHO and China’s national health strategies have emphasized the importance of integrating mobile health (mHealth) into public service delivery [13-15]. By leveraging digital technologies, mHealth can bridge gaps between research and practice by overcoming geographical and temporal barriers to deliver scalable, cost-effective interventions, including to resource-limited settings [16].

Further, the rapid advancement of artificial intelligence (AI) technologies has made it increasingly feasible to design interventions that integrate AI into mHealth apps. AI-enabled systems can ease workforce shortages by providing real-time support and interactions, automated risk assessments, and personalized recommendations. For example, a randomized controlled trial reported that an AI-powered digital platform for lifestyle change was effective in supporting weight loss among adults [17].

mHealth apps for child injury prevention have been piloted in high-income countries such as the United States [18-22], South Korea [23,24], and Australia [25], as well as in China [26-30]. Most of these interventions focus on delivering educational content via mobile platforms. However, several limitations have restricted their broader application in China [18-30]: (1) they primarily target preschool-aged children ages 3‐6 years, overlooking risk among infants and toddlers [18,19,21,24,27-30]; (2) they rely on standalone applications, creating limited user engagement and poor long-term adherence [18-29]; and (3) they typically require dedicated technical support, continuous user assistance, specialized intervention skills, and localized cultural and linguistic appreciation, infrastructure that is not embedded within the National Basic Public Health Service Program. Together, these limitations undermine scalability, sustainability, and integration into routine service delivery in China [18-30].

To address these gaps, we developed the Intelligent Child Unintentional-Injury Reduction & Education (iCURE) program that is integrated into China’s National Basic Public Health Service Program. iCURE is designed for health care providers to provide tailored advice on child injury prevention to caregivers via WeChat (Tencent), easing knowledge and temporal burden on providers and still conveying critical knowledge to caregivers. This protocol outlines a 12-month cluster randomized controlled trial to evaluate the effectiveness of iCURE in improving child injury–related knowledge, behaviors, and outcomes among caregivers of young children. If effective, iCURE offers a scalable and sustainable approach to incorporate child injury prevention into primary health care for young children and their parents across LMICs.

## Methods

### Study Design

A double-blind, 12-month, parallel-group cluster randomized controlled trial with 1:1 allocation ratio will be implemented in Changsha, Hunan Province, China. This study will strictly adhere to the SPIRIT (Standard Protocol Items: Recommendations for Interventional Trials) guidelines (Checklist 1)[31,32]. This protocol version is 1.0 and was enacted on August 1, 2024.

### Participant Recruitment

A 2-stage recruitment strategy will be conducted. First, 12 streets and towns were selected from 5 administrative districts in Changsha, including 3 urban districts (Kaifu, Yuhua, and Yuelu) and 2 rural areas (Ningxiang and Liuyang). Each district consisted of at least 2 streets and towns that were eligible for study recruitment (Figure 1). Eligible streets and towns had a primary health care institution present that (1) provides basic public health services for a population with over 2000 children younger than 5 years of age and (2) reports they are not involved in any active child injury prevention programs.

One health care provider per institution will facilitate participant recruitment through (1) face-to-face communication, leaflet distribution, and poster display during routine services; (2) digital advertisements and instructional videos shared through established communication platforms, such as WeChat groups; and (3) collaboration with local schools serving children aged 3 to 5 years, where teachers will distribute flyers to caregivers.

Families will be eligible if children (1) are aged ≤5 years at the time of baseline survey; (2) live with a primary caregiver who provides daily support; (3) reside in the selected study site; (4) have a caregiver aged ≥18 years who is literate, owns a smartphone, and provides informed consent; and (5) are not enrolled in other structured injury prevention programs. Children with severe illnesses requiring specialized care or hospitalization will be excluded.

**Figure 1. F1:**
[figure not shown]
Study flow diagram.

### Sample Size

Previous research reported a 12-month incidence of unintentional injury of 15.5% among children younger than 6 years of age in Changsha [33]. We hypothesize that the proposed mHealth intervention will reduce the injury incidence rate by 25% [34], with a design effect of 1.5 for the cluster sampling [35]. We also very conservatively assume 30% loss to follow-up [36]. Given these assumptions, a minimum sample size of 5178 children is needed to achieve 80% statistical power at a .05 significance level with a 1:1 allocation ratio between intervention and control groups (G*Power 3.1.9.7). Given that the actual values of certain parameters (eg, incidence rate and effect size) may be somewhat lower than assumed [28,34], we empirically expanded the sample size to recruit approximately 5600 children, with (2800 children from urban areas and 2800 from rural areas, including at least 350 children from each selected urban street and 700 from each rural town) within the constraints of available research resources. The 1:2 recruitment ratio of urban streets and rural towns is based on prior field experience, which suggests greater recruitment challenges in urban areas compared to rural ones.

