## Results

The study received funding in January 2023. Participant enrollment began in August 2024 and was completed in February 2025. A total of 6701 individuals completed baseline data, with 3110 allocated to the intervention group and 3591 to the control group (Table 2). The two groups somewhat differed in child age, place of residence, caregiver’s age, and education—the control group had higher proportions of children aged 3 to 5 years (69.7% vs 57.6%), residing in urban areas (61.3% vs 57.4%), caregivers aged 30 years and older (81.2% vs 74.9%) and receiving high or vocational school education and higher (85.7% vs 80.2%) than the intervention group (*P*<.05). The baseline 12-month injury incidence reported by caregivers was 8.86% (7.96-9.84) in the control group and 9.04% (8.06-10.11) in the intervention group.

By May 2025, 5,842 (87.2%) participants had completed the first follow-up survey.

**Table 2. T2:** Number of recruited caregivers and children by demographic characteristics (%).

Variables	Overall, n (%)	Control, n (%)	Intervention, n (%)	*P* value
Total	6701 (100.0)	3591 (100.0)	3110 (100.0)	
Child gender				>.99
Girl	3147 (47.0)	1686 (47.0)	1461 (47.0)	
Boy	3554 (53.0)	1905 (53.0)	1649 (53.0)	
Child age (years)				<.001
1	1047 (15.6)	468 (13.0)	579 (18.6)	
1-2	1358 (20.3)	619 (17.2)	739 (23.8)	
3-5	4296 (64.1)	2504 (69.7)	1792 (57.6)	
Place of residence				.001
Urban	3988 (59.5)	2203 (61.3)	1785 (57.4)	
Rural	2713 (40.5)	1388 (38.7)	1325 (42.6)	
Caregiver’s gender				.09
Female	5400 (80.6)	2922 (81.4)	2478 (79.7)	
Male	1301 (19.4)	669 (18.6)	632 (20.3)	
Caregiver’s age (years)				<.001
＜30	1458 (21.8)	677 (18.9)	781 (25.1)	
30-39	4343 (64.8)	2408 (67.1)	1935 (62.2)	
≥40	900 (13.4)	506 (14.1)	394 (12.7)	
Number of children in the family				.51
1	3010 (44.9)	1627 (45.3)	1383 (44.5)	
≥2	3691 (55.1)	1964 (54.7)	1727 (55.5)	
Caregiver’s education				<.001
Junior high school or lower	1131 (16.9)	514 (14.3)	617 (19.8)	
High or vocational school	1493 (22.3)	816 (22.7)	677 (21.8)	
College or higher	4077 (60.8)	2261 (63.0)	1816 (58.4)	

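### The 80% power claim makes no allowance for having only 12 randomized clusters, and at an injury incidence near the trial's own 9% baseline, power for a 25% reduction stays below 80% even with 6701 children

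*Protocol article*

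**What the plan says.** The Sample Size section of the protocol article gives these inputs:

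- Control incidence: "Previous research reported a 12-month incidence of unintentional injury of 15.5% among children younger than 6 years of age in Changsha".
- Effect: "We hypothesize that the proposed mHealth intervention will reduce the injury incidence rate by 25" percent.
- Clustering: "with a design effect of 1.5 for the cluster sampling". No intracluster correlation (ICC) or between-cluster coefficient of variation (CV) is given.
- Attrition: "We also very conservatively assume 30% loss to follow-up".

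From these, using G*Power and 1:1 allocation, it concludes that "a minimum sample size of 5178 children is needed to achieve 80% statistical power at a .05 significance level". It then concedes that incidence and effect may turn out somewhat lower and raises the target to about 5600, without restating power. Planned minimum cluster sizes are 350 per urban street and 700 per rural town.

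Under Participant Recruitment, "12 streets and towns were selected from 5 administrative districts in Changsha". Under Randomization and Blinding, these are the units randomized, stratified by administrative division. The Results report 6701 children (3110 intervention, 3591 control), 87.2% completing the first follow-up, and a caregiver-reported 12-month incidence at baseline of "8.86% (7.96-9.84) in the control group and 9.04% (8.06-10.11) in the intervention group". Power is not revisited.

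**The concern.** Two features of the article do not fit the 80%. First, the comparison of arms rests on 12 clusters, so it has at most 10 degrees of freedom. A calculation that multiplies an individual-level size by a design effect and keeps normal quantiles overstates power when clusters are this few. Second, the baseline incidence in the enrolled children is about 42% below the planning value (1 - 8.96/15.5, taking 8.96 as a rounded midpoint of the two arms), and neither arm's interval comes near 15.5%.

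At stake is how a non-significant result would be interpreted. If readers take 80% power for a 25% reduction as the trial's sensitivity, they may give a null finding more weight than it can bear. The article's conclusions look ahead to national and international scale-up, so the stated sensitivity matters.

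**Working it through.** **1. Reproducing 5178.** Two-sided 0.05, 80% power, pooled two-proportion formula, 15.5% versus 11.6% (11.625% rounded): 1208 per arm. Then 2 × 1208 × 1.5 / 0.7 = 5177.1, rounded up to 5178. Without rounding the second proportion the result is 1225 per arm and 5250 in total. The plan's figure is right for its inputs.

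**2. Same inputs, 12 clusters.** With N enrolled, loss L and design effect DE, the effective number per arm is n = N(1 - L)/(2·DE), and

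δ = (p1 - p2) / √[(p1q1 + p2q2)/n].

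Normal-theory power is Φ(δ - 1.96). Few-cluster power is the probability that a noncentral t on 10 df with noncentrality δ exceeds 2.228.

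- N = 5178: n = 5178 × 0.7/3 = 1208.2; δ = 0.03875/0.01391 = 2.79. Power is 80% (normal) or **71%** (t, 10 df). A beta-binomial simulation of a cluster-level t test also gave 71%, with a type I error of 5%.
- N = 5600: n = 1306.7; δ = 2.90. Power is 83% (normal) or **74%** (t, 10 df).

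**3. What the design effect implies.** The document gives no ICC, so this step is an assumption. At 5178 × 0.7/12 = 302 analysed children per cluster, DE = 1.5 implies ICC = 0.5/301 = 0.00166. The extra children enter the same 12 clusters, so three conventions are reasonable at 6701:

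- DE held at 1.5.
- ICC held at 0.00166: DE = 1 + 390 × 0.00166 = 1.65 at 30% loss (391 per cluster), or 1 + 486 × 0.00166 = 1.81 at 12.8% loss (487 per cluster).
- Between-cluster CV held constant: CV² = 0.00166 × 0.8644/0.1356, so CV = 0.103. At 8.86% incidence the ICC falls to about 0.0009, and DE is about 1.35 (30% loss) or 1.43 (12.8% loss).

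**4. Power at 6701 for a 25% reduction, control incidence 8.86%.** Example with DE 1.5, 30% loss and the actual arm sizes: effective numbers are 3591 × 0.7/1.5 = 1675.8 and 3110 × 0.7/1.5 = 1451.3; δ = 0.02215/0.00954 = 2.32; power is 64% (normal) or 55% (t, 10 df). All cases, normal / t on 10 df:

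| Held constant | 30% loss | 12.8% loss |
|---|---|---|
| DE 1.5 | 64% / 55% | 74% / 65% |
| ICC 0.00166 | 60% / 52% | 66% / 57% |
| Between-cluster CV 0.103 | 69% / 60% | 76% / 67% |

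The ranges are therefore 52-69% and 57-76%. The same grid at 12% incidence spans about 66-86%. At 15.5% with 30% loss, the t-based figure is 82% (DE 1.5) or 78% (ICC constant).

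**5. Two cross-checks.** The plan's own formula at 8.86% needs 2287 per arm, so 2 × 2287 × 1.5/0.7 ≈ 9800 children. With DE 1.5 and 6701 children, the lowest control incidence that keeps 80% power is about 12.6% (normal) or 15.0% (t, 10 df) at 30% loss, and 10.3% or 12.3% at 12.8% loss.

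**6. Not in these ranges.** The planned unequal clusters (2800/350 = 8 and 2800/700 = 4) raise a design effect of 1.5 to about 1.56. Stratification may leave fewer than 10 df: at 8.95%, DE 1.5 and 30% loss, 6 df gives 50% against 56% on 10 df.

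**The case against.** Several points on the other side have weight.

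- **The statement is conditional and prospective.** The section ties its figure to stated assumptions and admits that they may be optimistic. The protocol version dates from August 2024, when enrolment began, so the baseline data could not have informed it. This stands: the article does not claim 80% as achieved power. But it prints the planning figure and the baseline incidence together without reconciling them, and the few-cluster problem exists at the planning inputs regardless of later data.
- **Baseline is a weak proxy.** Follow-up injuries are collected quarterly with prompts for minor events. The youngest row of Table 2, apparently infants, holds 15.6% of children, who would have had less than 12 months of exposure at baseline. Both could push follow-up incidence above 9%. This stands, and is why results at 12% and 15.5% are shown.
- **Thirty percent loss is pessimistic.** The 87.2% retention is encouraging, but it covers only the first of four follow-ups. Hence both loss figures are shown.
- **The analysis differs from a plain t test.** A covariate-adjusted mixed model after stratified randomization may recover some precision. It does not create more clusters.
- **Confidence intervals will be reported.** They would show which effects remain compatible with a null result. This lessens the harm but does not correct the power claim.

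A reader might infer that 5178 is a miscalculation, or that power is simply 52-64%. The documents support neither. The figure reproduces, and that range holds only for 30% loss with a fixed design effect or ICC at about 9% incidence; it leaves out observed retention and the constant-CV case.

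**Conclusion.** The point holds as a fault in the power statement, not in the arithmetic. The stated 80% at the .05 level does not follow for a 12-cluster trial: on the plan's own inputs it is about 71% at 5178 and 74% at 5600. At 6701 and 15.5% incidence, over-enrolment brings t-based power back to about 78-82% with 30% loss, so the few-cluster loss is largely offset there.

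The main exposure is incidence. If follow-up resembles the 8.86-9.04% baseline, every combination in the table falls short of 80%. The risk ratio detectable with 80% power is then about 0.66-0.71 on 10 df, or 0.69-0.74 by normal theory, instead of the hypothesized 0.75. These figures rest on baseline recall as a proxy, on a clustering parameter back-solved from a design effect of 1.5, and on 10 df as the few-cluster reference. Where follow-up incidence will fall between 9% and 15.5% cannot be settled from the documents.

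**What to change.** Rewrite the power paragraph, with no further enrolment:

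- State that 12 clusters are randomized.
- Give the ICC or between-cluster CV assumed and its basis, and account for unequal cluster sizes.
- Report few-cluster (t-based) power for a 25% reduction, and the risk ratio detectable with 80% power, for the 6701 enrolled children over control incidences of 9-15.5% and losses of about 13-30%.
- Replace the 80% claim with that grid. Keep 5178 and 5600 only as the historical planning figures, labelled as normal-theory sizes.

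The cost is a recalculation and new wording. The downside is that the stated power becomes less favourable. Design, conduct and analysis are unaffected.

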### Intervention

The iCURE program is designed as an expert system, defined as a computer-based system that simulates the decision-making ability of a human expert, integrating the latest evidence-based knowledge on child injury prevention and applying rules of logic to provide context-specific guidance and tailored education to caregivers [37]. Its development is guided by expert system methodologies and the intervention mapping framework [38]. The design incorporates core principles from injury prevention and behavior change theories, along with empirical evidence and key stakeholders’ perspectives [39,40]. These components were integrated through a systematic development process involving literature review, needs assessment, and expert consultation [38]. The program applies algorithms such as keyword matching, text similarity analysis, decision tree models, and rule-based logic to deliver personalized recommendations and support [37,40-42].

A pilot study was conducted to assess the feasibility and operational performance of the iCURE program. The findings from the pilot were used to optimize its design and implementation, including improvements in system stability, registration flow, reward mechanisms, and data quality control.

### Key Components and Content of the iCURE Program

The iCURE program consists of 2 components, a WeChat service account for caregivers and a web-based platform for health care providers (Figure 2 and MultimediaAppendices 1  2). This dual-platform approach facilitates information delivery and, crucially, supports caregiver-provider interaction.

**Figure 2. F2:**
[figure not shown]
The functional modules and operational flowchart diagram of the mHealth intervention for child injury prevention.

The WeChat service account serves as the main channel for delivering intervention content to caregivers. The web-based platform is only accessible to health care providers, who support the system by managing and customizing educational content, monitoring caregiver engagement, and tracking self-reported injury events. All data are saved securely once collected and can be visualized on the platform. Providers and researchers can also export relevant data, including risk assessment outcomes, injury events, and intervention engagement, as needed (Multimedia Appendix 1).

The WeChat service account for caregivers comprises 5 key modules:

Injury risk assessment: a comprehensive child injury risk assessment questionnaire, developed based on validated tools [43-47], to assess child age, caregiver and child behaviors, and environmental risk.Instant feedback: upon completing the risk assessment, participants receive immediate feedback and tailored recommendations generated by an integrated expert classification system and a decision tree model. This system stratifies children into low or moderate risk or high risk, which supports further personalized prevention strategies. For research purposes, participants who are randomly assigned to the control group will complete the assessment but will not receive feedback. Caregivers of children in the intervention group who are identified by the system as “high risk” will receive item-specific risk reports. This individualized risk profile will guide the dissemination of AI-tailored education materials for each child.Injury reporting: caregivers are encouraged to report any injury events their children experienced during the study period. The module facilitates timely documentation and monitoring of injury events.Interactive questions and answers (Q&A): caregivers may submit injury prevention questions through the platform’s real-time Q&A interface, which provides instant computer-generated and automated responses. The iCURE platform uses a hybrid natural language processing approach that combines keyword matching and text similarity analysis to retrieve and deliver relevant, automated responses from a curated injury prevention knowledge base created by the research group.Tailored education: personalized educational content on child injury prevention is delivered in various formats (eg, text, images, long-form infographic post, flyers, and short videos). Delivery frequency is determined by a rule-based decision logic algorithm and tailored to the child’s risk level; caregivers of low-risk children receive content once per week, while those with higher-risk children receive it 2 or 3 times per week.

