### Outcomes

The primary outcome is unintentional injury incidence, calculated as:

$$\frac{Number\;of\;children\;with\;injuries\;during\;the\;12-month\;study\;period}{Total\;number\;of\;children}\times 100\%$$

Injury events will be identified based on established criteria from previous studies [48], defined as any of the following: (1) receiving medical attention at a health care facility and being diagnosed with a specific injury; (2) receiving first aid from a nonmedical responder (eg, family member and teacher), such as wound dressing or bandaging; and (3) missing school for more than half a day due to an injury. We will also compare injury rates at 3-month intervals to assess the effect over time.

In addition, several secondary outcomes will be assessed:

(1) Change in child injury risk level: A 46-item questionnaire will assess children’s risk of unintentional injury, classifying children as low-to-moderate or high risk. The questionnaire was adapted from existing validated instruments and covers 8 common types of injuries: drowning (5 items), road traffic injuries (6 items), choking (6 items), falls (6 items), burns and scalds (6 items), poisoning (5 items), animal bites (5 items), and sharp and blunt object or foreign body injuries (7 items) [43-47].

(2) Change in caregiver supervision behavior score: Caregivers’ caregiver supervision behavior will be measured using a simplified version of a validated 5-item questionnaire, with responses rated on a 5-point Likert scale [49]. Items overlapping with the child injury risk assessment questionnaire were excluded to avoid redundancy.

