### Data Analysis

Data will be analyzed following intention-to-treat principles and including all participants as originally assigned, regardless of adherence. Descriptive analysis (mean, SD, median, IQR, and proportion) will be used to describe baseline characteristics by groups. Differences in unintentional injury incidence across 5 timepoints (baseline, 3, 6, 9, and 12 mo) and other outcomes at 2 timepoints (baseline and 12 mo) will be examined using rank-sum tests for ordinal outcomes, chi-square tests for categorical outcomes, and independent 2-sample *t* tests for continuous outcomes. Within-group changes over time will also be evaluated.

Generalized linear mixed models with a Poisson link function will be used to compare the 12-month injury incidence between groups, adjusting for baseline covariates and accounting for clustering at the street or town level. Risk ratios and 95% CIs will be reported. Generalized estimating equations will also be used to assess repeated measures of injury incidence across follow-up timepoints, providing population-averaged estimates while accounting for within-subject and within-cluster correlations. Secondary outcomes, including changes in injury risk levels and caregiver supervision behaviors, will be analyzed using regression models appropriate to the type and distribution of the variable. User engagement indicators will be included as covariates of the effectiveness analysis model.

Two sets of sensitivity analyses will be performed to assess the robustness of findings: (1) per-protocol analyses and (2) models excluding participants with missing primary outcome data. Missing data will be documented and addressed using appropriate statistical methods as needed.

This study will adhere to the CONSORT (Consolidated Standards of Reporting Trials) 2025 [52] statement to perform data analysis and report results.

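### The between-arm tests named for the two secondary outcomes are unadjusted, and no age or cluster adjustment is stated for them, although the arms differ in child age and age may bear on the risk level

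*Protocol article*

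**What the plan says.** All references are to the protocol article.

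- **Key Components and Content of the iCURE Program** (module list): the risk questionnaire is designed "to assess child age, caregiver and child behaviors, and environmental risk". An expert classification and decision tree then produces the result: "This system stratifies children into low or moderate risk or high risk".
- **Outcomes**: the first secondary outcome is change in this level, from a 46-item questionnaire "classifying children as low-to-moderate or high risk". The items are listed by eight injury types. The second is change in a caregiver supervision score.
- **Data Analysis**: alongside injury incidence, the plan compares "other outcomes at 2 timepoints (baseline and 12 mo") using rank-sum, chi-square and two-sample t tests. It then adds: "Secondary outcomes, including changes in injury risk levels and caregiver supervision behaviors, will be analyzed using regression models appropriate to the type". Baseline-covariate adjustment is stated for the primary mixed model. Clustering by street or town is stated for that model, and within-cluster correlation for the repeated-measures model of injury incidence. Neither is stated for the secondary outcomes. A general sentence brings engagement indicators in as covariates, but that is not adjustment for baseline differences.
- **Results, Table 2**: children aged 3 to 5 years make up 69.7% of the control arm and 57.6% of the intervention arm, P<.001.

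**The concern.** The only between-arm comparisons that the article spells out for the secondary outcomes are unadjusted tests that treat children as independent, in a trial randomised by street or town with a reported age imbalance. Child age is named first among the things the risk assessment covers, and child behaviours, also covered, may change with development. If risk level is related to age by either route, two things follow:

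- A chi-square test on 12-month risk level partly compares a younger arm with an older one.
- A comparison of change can pick up ageing, because the arms start from different ages and a two-level outcome need not respond equally at every age.

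At stake is a small apparent benefit or harm on a secondary outcome that iCURE did not cause, tested with a standard error that ignores clustering.

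**Working it through.** **1. Reproduce Table 2.** Control: 468, 619 and 2504 of 3591 = 13.0%, 17.2%, 69.7%. Intervention: 579, 739 and 1792 of 3110 = 18.6%, 23.8%, 57.6%. These match the printed figures. The youngest band is printed as 1 and is taken to mean under 1 year. Pearson chi-square is 106.4 on 2 df (P about 8e-24, ignoring clustering).

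Under 3 years: intervention (579 + 739)/3110 = 42.4%; control (468 + 619)/3591 = 30.3%.

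**2. Does the questionnaire contain an age item?** Outcomes lists 5 + 6 + 6 + 6 + 6 + 5 + 5 + 7 = 46 items, which uses up the whole questionnaire. The module list nevertheless says that it assesses child age. Age could be a decision-tree input, a way of routing to items, or only a recorded variable. The article does not say which.

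**3. Ageing alone, with no treatment effect.** Assume that in 12 months all of the youngest band move to 1-2, half of the 1-2 band move to 3-5, and the rest keep their class. Let r1, r2, r3 be the probability of high risk in the three bands. The article gives none of these, so all are assumptions.

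- Change in an arm = p1(r2 - r1) + 0.5·p2(r3 - r2), where p1 and p2 are the arm's shares in the two younger bands.
- Between-arm difference in change = 0.0558(r2 - r1) + 0.0326(r3 - r2), from 0.1862 - 0.1303 and half of 0.2376 - 0.1724.
- Share still under 3 at 12 months: (579 + 739/2)/3110 = 30.5% and (468 + 619/2)/3591 = 21.7%, a gap of 8.8 points. The unadjusted 12-month difference is therefore 0.088(r2 - r3).

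| Assumed high risk, youngest / 1-2 / 3-5 (%) | Change, intervention | Change, control | Difference in change | Difference at 12 months |
|---|---|---|---|---|
| 20 / 20 / 20 | 0 | 0 | 0 | 0 |
| 20 / 40 / 20 | 1.35 | 0.88 | +0.5 | +1.8 |
| 20 / 40 / 30 | 2.54 | 1.74 | +0.8 | +0.9 |
| 20 / 40 / 40 | 3.72 | 2.61 | +1.1 | 0 |
| 10 / 50 / 30 | 5.07 | 3.49 | +1.6 | +1.8 |
| 40 / 30 / 20 | -3.05 | -2.17 | -0.9 | +0.9 |
| 60 / 40 / 20 | -6.10 | -4.33 | -1.8 | +1.8 |

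Differences are intervention minus control, in percentage points. A variant with 30/50/30% and 10% at age 6 and over, moving a third of the oldest band up, gives +1.3 points in change.

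**4. When it cancels.** If every child's probability shifts by the same amount c whatever the age, the difference in change is c - c = 0.

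**5. Scale.** Assume 30% high risk. Take the design effect of 1.5 and the 30% loss from Sample Size (the design effect was set for injury incidence). The standard error of a 12-month difference is sqrt(1.5 × 0.3 × 0.7 × (1/(0.7 × 3110) + 1/(0.7 × 3591))) = 0.0164, or 1.6 points. Without the design effect it is 1.3 points, which is roughly what an unclustered test would use.

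**The case against.** The strongest reply is that the link from age to the outcome is not documented. Naming age among the things assessed does not make it a determinant of the low-to-moderate or high class, and the 46 items leave none for age. If items or cut-offs are age-specific, the level may already allow for age. This stands: age as a classifier input is an inference.

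Second, ageing is common to both arms and cancels in a comparison of change unless its effect differs by age. This also stands for change. It does not help the unadjusted 12-month test, where any difference in risk between children under and over 3 passes straight through.

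Third, an article need not list covariates, and the full analysis plan may name age. Data Collection says that baseline variables were chosen partly as potential confounders, and the Discussion claims control for confounding. That is fair, so the point is not that covariates are unlisted. The point is that the article does name a method for these outcomes, and it is an unadjusted one, while adjustment is stated for the primary model only.

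A reader might go further in three ways that the document does not support:

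- That the risk level moves as every child gets a year older. A two-level result changes only for children who cross a threshold, and under the banding above the 3-5 group (64% of children) does not move.
- That within-group change is offered as evidence of effect. Data Analysis says only that it will be evaluated.
- That the supervision score has the same age dependence. Nothing in the article makes age part of that score. It is covered here because it shares the same unadjusted test and unstated clustering.

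**Conclusion.** The point holds as a modest improvement to the analysis of the secondary outcomes. The named tests ignore both the reported age imbalance and the cluster design, and the role of age in the risk level is described inconsistently.

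No single size can be given, because the article reports no risk level by age. Under assumed age-band steps of 10 to 40 points, the artefact in change runs from about -1.8 to +1.6 points, of either sign. It is 0 if risk does not depend on age or if ageing acts equally at all ages. That is at most about one standard error (1.6 points, itself assuming 30% high risk, 30% loss and a design effect of 1.5).

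A reader might infer a larger artefact in change, 0.9 to 3.5 points, by multiplying the 8.8-point gap in band crossing by steps of 10 to 40 points. That assumes the same step in the same direction at both crossings and leaves out zero. The 3.5-point end would need an 80-point gap in high-risk probability between infants and children aged 3 to 5, which nothing in the document supports. The primary outcome is not affected by this point.

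**What to change.** In Data Analysis, make the main between-arm comparison of each secondary outcome a model of the 12-month value (risk level; supervision score). Adjust it for that outcome's baseline value and for baseline child age, in months if held and otherwise in the Table 2 bands, and account for clustering by street or town. State that the chi-square, rank-sum and t tests are descriptive.

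Reconcile the module list with Outcomes: say whether child age sets the risk class, routes to items, or is only recorded, and which age is used at 12 months. Only if age is a direct input to the classification, add a sensitivity analysis of an item-based result that excludes age. Re-scoring the 12-month visit with age frozen at baseline is not advised as the general remedy. It may apply infant rules to a toddler and may not be possible if items are routed by age.

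The cost is wording. Baseline age, risk level and supervision score are already collected, and no visit, item or participant is added. With age adjusted for, the component worked out above is removed in expectation.
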